#### Cost-effectiveness analyses

The economic evaluation will consist of a cost-effectiveness analysis and a cost-utility analysis, both done from a societal perspective [50]. The cost-effectiveness ratio will represent the costs per significantly improved participant, while the cost-utility analysis will represent the costs per additional quality-adjusted life year (QALY). The time horizon will be life time. As the study period is limited in time, cost and effect will be modelled in time, using the assumption that the spontaneous recovery is 2 years. The effects of this assumption on the cost-effectiveness ratio will be tested by testing the scenarios of spontaneous recovery after 6 months, 1 year and 5 years.

Costs will be estimated from a societal perspective and will thus include the costs related to the intervention, all other healthcare costs and non-healthcare costs during the time horizon of the study. Healthcare consumption will be measured with the MCQ. Healthcare consumption includes all non-disease specific healthcare used in the previous 3 months, such as visiting the general practitioner or other healthcare providers, emergency room visits, hospitalisation, and medication use. Then, the guidelines as descripted by the Dutch Manual on Cost Investigations will be used to calculate the healthcare costs [46]. For healthcare where no guideline or standard prices are available, real cost prices will be determined or, when available, derived from the health care provider administration.

QALYs will be calculated from EQ-5D health states using the Dutch EQ-5D tariff [47]. Non-parametric bootstrap simulations will be used to estimate uncertainty intervals around the ICERs, in order to deal with the most likely skewed distributions of costs. Cost-effectiveness acceptability curves will be calculated to show the probability that the intervention is cost-effective in comparison with the control group, given varying thresholds for the willingness-to-pay for gaining one unit of effect, i.e. a QALY or a significantly improved participant. The robustness of the results will be explored using one-way sensitivity analyses in which the input variables for assessing both cost and effectiveness are varied.

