
### Aims

The primary aim of the CAncer REcurrence Self-help Training [CAREST] randomised controlled trial is to evaluate the effectiveness and cost-effectiveness of the online CBT-based self-help training “Less fear after cancer” [in Dutch: “Minder angst bij kanker”] in reducing FCR in women with curatively treated breast cancer (breast cancer survivors), compared to usual care. Specific hypotheses are that:FCR severity reduces more in the online self-help condition compared to the usual care condition between baseline and follow-up (3 months). This effect will sustain 9 and 24 months after baseline. Small effect sizes are expected.Health care costs reduce more in the online self-help condition compared to the usual care condition between baseline and 24 months after baseline.Psychological distress reduces more in the online self-help condition compared to the usual care condition between baseline and 3 months after baseline. These effects will sustain 9 and 24 months after baseline.

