### Strengths and weaknesses

In the proposed study, an online CBT-based self-help training will be compared with care as usual. To the best of our knowledge, this is the first study to evaluate an online self-help training for FCR in breast cancer survivors. Using the internet, this intervention provides a novel and easy-accessible approach to reduce the impact of FCR at an early stage. In the long term this study may contribute to early prevention of FCR. Moreover, a health economic evaluation is included in the trial, to assess the cost-effectiveness of the online self-help training up to 24 months. The 24 months follow-up period strengthens the study, whereas many studies only include follow-up periods up to 12 months. The results of the study will provide information on the possible strengths and benefits of online self-help training for FCR in breast cancer survivors. However, since both the intervention and the control group are allowed to receive usual (psychological) care during the study, the expected effects are small. Inclusion of women with all levels of FCR, ranging from no FCR to considerable FCR, may also decrease the effectiveness of the online self-help training. Nevertheless, this design provides the opportunity to predict who benefits most from the intervention. Therefore, this trial will provide clinically relevant information. Considering the lack of intervention research for FCR in breast cancer patients, this study will contribute to the body of knowledge about how to best support this large and growing group. Research into alternative, long-term effective treatment options for this group will be of great clinical value. The eventual goal of the proposed study is to implement an easy accessible, evidence-based and cost-effective intervention for FCR in women who benefit most from these kind of online self-help interventions, within the follow-up care of breast cancer patients in the Netherlands.

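### Bootstrap intervals around the ICER are likely to be uninterpretable if the effect difference is not clearly separated from zero, which is plausible for QALYs; net benefit from the same replicates avoids this

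*Protocol article*

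**What the plan says.** All places are in the protocol article.

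- **Cost-effectiveness analyses, uncertainty.** The plan states "Non-parametric bootstrap simulations will be used to estimate uncertainty intervals around the ICERs", and the reason given is "in order to deal with the most likely skewed distributions of costs". It does not mention the sign of the ratio or replicates on both sides of zero effect.
- **Cost-effectiveness analyses, ratios.** There are two: "The cost-effectiveness ratio will represent the costs per significantly improved participant", and a cost-utility ratio per QALY. The numerator is wide: "Costs will be estimated from a societal perspective and will thus include the costs related to the intervention", together with all other healthcare and non-healthcare costs.
- **Cost-effectiveness analyses, second measure.** "Cost-effectiveness acceptability curves will be calculated to show the probability that the intervention is cost-effective", over a range of willingness-to-pay thresholds and for both effect units.
- **Aims.** Cost-effectiveness is part of the primary aim. The cost hypothesis is "Health care costs reduce more in the online self-help condition compared to the usual care condition between baseline and 24 months after baseline". Under the hypothesis on severity of fear of recurrence, "Small effect sizes are expected".
- **Strengths and weaknesses.** Because usual care is open to both groups, "the expected effects are small".

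No cost difference, QALY difference or standard error for either is given.

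**The concern.** An ICER divides one uncertain difference by another, which causes two problems that skewness does not explain and resampling does not cure.

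First, the sign of the ratio is ambiguous. A negative value can mean cheaper and better or dearer and worse. A positive value can mean dearer and better or cheaper and worse. Second, a denominator near zero sends replicates to very large values of either sign. A percentile interval sorts these values as if larger always meant less favourable, which is untrue once the effect difference changes sign between replicates.

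At stake is how the uncertainty of the economic result is presented. A wide interval spanning zero could be read as showing nothing when the same replicates lean clearly one way. Its limits could also be quoted as cost-effectiveness thresholds that they are not. The analysis of severity of fear of recurrence is not touched.

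**Working it through.** The article gives no ICER or interval, so there is no figure of its own to reproduce. Write dC for the cost difference, dE for the effect difference, ICER = dC/dE, and NMB = λ·dE − dC, with λ = 20,000 per QALY assumed.

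**1. Does the ratio have an order?**

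| dC | dE | ICER | NMB |
|---|---|---|---|
| −1000 | +0.05 | −20,000 | +2000 |
| +1000 | −0.05 | −20,000 | −2000 |
| −1000 | +0.01 | −100,000 | +1200 |

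The first two rows share an ICER but lead to opposite decisions. The first and third are both cheaper and better, yet the more negative ratio belongs to the less favourable result.

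**2. How often does the effect change sign?** For an effect z standard errors above zero, the opposite-sign share is Φ(−z): 31 % at z = 0.5, 16 % at 1, 7 % at 1.5 and 0.1 % at 3.

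**3. What happens to the interval?** Assumed: dC normal with mean −100 and SE 200; QALY difference with SE 0.01; independent draws.

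| QALY effect | 95 % interval of dC/dE | 95 % interval of NMB |
|---|---|---|
| 0.01 (1 SE) | about −182,000 to +163,000 | 300 (−254 to 854) |
| 0.03 (3 SE) | about −23,000 to +12,000 | 700 (145 to 1255) |

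The NMB limits follow directly. The SE is √((20,000 × 0.01)² + 200²) = 283 and 1.96 × 283 ≈ 554, so 300 ± 554 and 700 ± 554, up to rounding.

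At 1 SE the replicates fall 26 % dearer and better, 58 % cheaper and better, 11 % cheaper and worse, and 5 % dearer and worse. Changing the mean cost difference to +100 still gives about −163,000 to +181,000, so the denominator alone is enough.

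**4. Does an actual bootstrap with skewed costs behave the same way?** Assumed: QALY SD 0.3, mean cost 5000, lognormal costs with coefficient of variation 1.5, cost–QALY correlation −0.3, 227 per arm, 200 simulated trials of 2000 resamples. The SE of the QALY difference is 0.3 × √(2/227) = 0.028.

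| dE (in SE) | dC | cheaper and better | median limits of dC/dE |
|---|---|---|---|
| 0.02 (0.7) | −300 | 46 % | −248,000 to +234,000 |
| 0.05 (1.8) | −1000 | 81 % | −117,000 to +42,000 |
| 0.10 (3.6) | −1000 | 89 % | −27,000 to +2,100 |

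Resampling does not remove the problem at small effects. It fades once the effect is about 3 SE or more from zero. In the last row nearly all remaining resamples are dearer and better, so the effect sign is stable.

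**5. How exposed is the improved-participant ratio?** On severity itself, d = 0.3 with 227 per arm (Sample size calculation) is 0.3 × √(227/2) = 3.2 SE, an opposite-sign share of 0.07 %. Suppose improvement is a cut on a normal score shifted by 0.3 SD, with an assumed control response p₀ of 10 to 50 %. Then p₁ = Φ(Φ⁻¹(p₀) + 0.3) and z = (p₁ − p₀)/√[(p₀(1−p₀) + p₁(1−p₁))/n].

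- n = 227: z is about 2.0 to 2.5, opposite sign 0.5 to 2.3 %.
- n = 147 (the 35 % loss cited from earlier studies; 227 × 0.65 ≈ 147): z is about 1.6 to 2.1, opposite sign 2 to 5 %.

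The exposure is real but smaller than it may be for QALYs.

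**The case against.** A reader might infer that the trial's own hypotheses place the ICER in the cheaper-and-better quadrant, so its interval is bound to be meaningless. The documents do not support that, for these reasons:

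- The cost hypothesis concerns healthcare costs. The numerator is societal and includes the intervention, so a dearer-and-better result remains possible.
- Small effects are stated for severity of fear of recurrence. Nothing is said about the expected size for QALYs or for the share improved.
- The sign of the cost difference does not by itself spoil the interval. If the effect difference is positive in nearly all replicates, ICER < λ is equivalent to NMB > 0 whatever the cost sign. The upper limit is then the threshold at which the acceptability curve reaches 97.5 %, and in the 3 SE illustration it does so. The sizes of negative ratios remain unordered, but that limit can be read.
- The acceptability curves count replicates with positive net benefit at each threshold and are valid in every quadrant. The economic conclusion would not lack a sound uncertainty statement.

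All of these stand, and they limit the point to one reported quantity.

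It can also be said that the article does not name the percentile method, and that handling of quadrants belongs in a fuller plan. That is fair for the construction of the interval, and its absence is not the complaint. But placing an interval on the ratio is a stated choice with a stated reason, and the reason addresses a different problem.

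**Conclusion.** The point holds in a limited and conditional form. An interval on the ICER is likely to be uninterpretable if the effect difference is not clearly separated from zero, so that replicates spread over quadrants with opposite effect signs. Skewed costs justify a bootstrap, but not one summarised on the ratio scale.

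The condition is plausible for the QALY ratio. It is less so for the improved-participant ratio, provided that d = 0.3 is achieved and carries over to the response definition. The acceptability curves and the clinical primary outcome are unaffected.

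No single size can be given. Every cost and QALY input above is assumed, and the results run from intervals hundreds of thousands wide at about 1 SE to readable ones at about 3 SE. The ordering argument in step 1 needs no such inputs. This is a worthwhile improvement to one reported interval and does not show that the economic evaluation is invalid.

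**What to change.** Replace the commitment to ICER intervals with the following, all from the same bootstrap replicates and for both effect units:

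1. Bootstrap 95 % intervals for incremental cost and incremental effect separately.
2. The cost-effectiveness plane with the share of replicates in each quadrant.
3. Incremental net monetary benefit with its bootstrap 95 % interval at willingness-to-pay values stated in advance.
4. The acceptability curves, as already planned.
5. The ICER as a point estimate, with an interval only if essentially all replicates have an effect difference of the same sign.

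The cost is a change of wording and a few extra lines of output. No data collection, sample size or resampling changes.

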## Discussion

FCR is one of the most common long-term consequences of surviving cancer, with a major impact on personal, family, and professional life and is associated with considerable healthcare costs. In order to ensure the availability of affordable evidence-based psychological interventions for FCR in the future, research on cost-effective interventions for FCR is needed. This is especially relevant for psychological care in breast cancer survivors, as breast cancer is the most prevalent form of cancer in women and the prevalence is still increasing, together with the healthcare costs [1]. Online self-help training may be an efficient and cost-effective way to offer psychological treatment for this group. Moreover, online self-help may provide easy-accessible treatment for the large group of breast cancer survivors with low to moderate FCR, diminishing the number women in need of face-to-face therapy. Therefore, the CAREST-study has been designed to evaluate the effectiveness and cost-effectiveness of an online self-help training for FCR.

### Strengths and weaknesses

In the proposed study, an online CBT-based self-help training will be compared with care as usual. To the best of our knowledge, this is the first study to evaluate an online self-help training for FCR in breast cancer survivors. Using the internet, this intervention provides a novel and easy-accessible approach to reduce the impact of FCR at an early stage. In the long term this study may contribute to early prevention of FCR. Moreover, a health economic evaluation is included in the trial, to assess the cost-effectiveness of the online self-help training up to 24 months. The 24 months follow-up period strengthens the study, whereas many studies only include follow-up periods up to 12 months. The results of the study will provide information on the possible strengths and benefits of online self-help training for FCR in breast cancer survivors. However, since both the intervention and the control group are allowed to receive usual (psychological) care during the study, the expected effects are small. Inclusion of women with all levels of FCR, ranging from no FCR to considerable FCR, may also decrease the effectiveness of the online self-help training. Nevertheless, this design provides the opportunity to predict who benefits most from the intervention. Therefore, this trial will provide clinically relevant information. Considering the lack of intervention research for FCR in breast cancer patients, this study will contribute to the body of knowledge about how to best support this large and growing group. Research into alternative, long-term effective treatment options for this group will be of great clinical value. The eventual goal of the proposed study is to implement an easy accessible, evidence-based and cost-effective intervention for FCR in women who benefit most from these kind of online self-help interventions, within the follow-up care of breast cancer patients in the Netherlands.

## Trial status

Inclusion has started in April 2014. Inclusion is estimated to take up to two years, with one to two years follow-up. Final results are expected around summer 2017.

## Abbreviations

ACT, Acceptance and Commitment Therapy; AIC, Akaike Information Criterion; BIC, Bayesian Information Criterion; CAREST, CAncer REcurrence Self-help Training; CBT, Cognitive behavioural therapy; CMO, Medical Ethics Committee; CONSORT, Consolidated Standards of Reporting Trials; CWS, Cancer Worry Scale; EQ-5D, EuroQol-5D; FCR, Fear of Cancer Recurrence; FCRI, Fear of Cancer Recurrence Inventory; FCRI-NL, Dutch version of the Fear of Cancer Recurrence Inventory; ITT, intention-to-treat; MBCT, Mindfulness Based Cognitive Therapy; MBSR, Mindfulness Based Stress Reduction; MCQ, Medical Consumption Questionnaire; PDQ-BC, Psychosocial Distress Questionnaire-Breast Cancer; QALY, quality-adjusted life year; RCT, Randomised Controlled Trial; REML, restricted maximum likelihood; SPIRIT, Standard Protocol Items: Recommendations for Interventional Trials; VAS, visual analogue scale
